**Figure 2 figure2:**
[figure not shown]
Apptivate main menu and workout view.

### Contextual Bandits Algorithm

The contextual multiarmed bandit model used in this study is a type of reinforcement machine learning approach, which uses experimentation to learn about users’ performance and recommend the best potential option. As shown in Figure 3, the algorithm incorporates users’ past outcomes (target) and context (features) to assign probabilities to each treatment option and recommend the best possible treatment in the future (higher likelihood of success, noted in green). Once given a recommendation, users respond (either positively or negatively in this case), and this information is used for further training the algorithm for the next interaction. There are several algorithms developed to solve CB models, differing in how probabilities for each option are updated (learning) and the degree of exploration (randomness) involved in providing users with different options.

**Figure 3 figure3:**
[figure not shown]
Contextual bandit algorithm design.

Formally, at each round *t*=1*,...,T*, we observe the individual’s context (*x_t_* ∈ X), from which the algorithm recommends an action (*a_t_* ∈ A), and the environment reveals a reward (*r_t_* ∈ [0*,*1]). Intuitively, the algorithm needs to choose the policy *π* ∈ Π that maximizes the cumulative reward , where Π is a mapping of all policies relating context to actions (Π ⊆ {X → A}). We can define the average reward of a policy *π* as:

Based on this idea of expected cumulative reward, we can then determine the cumulative regret from a given policy as the difference between the observed reward for the recommended action and the expected reward of the recommended action:

In this setup, the different types of CB algorithms differ in their proposed approaches to achieve regret minimization. In practice, some algorithms will be better suited for different empirical applications, depending on the number of rounds, the possible set of actions, and the heterogeneity in the context from which the algorithm learns to allocate the best recommendation [31]. As such, the pilot phase is critical to determining the best approach for this experiment.

### Study Design

This study poses two main hypotheses: (1) goal personalization with CBs decreases the intention-behavior gap for some users, and (2) the effectiveness of such goal personalization on behavior is mediated through individual choice. To explore these hypotheses, participants will be randomly assigned to 1 of 3 groups: choice-driven, data-recommended, or data-driven.

The target population are university students (both undergraduate and graduate) from different institutions, allowing for differences in region, language, and time zone of the participants. Randomization will be stratified by baseline demographic factors, including household composition, income, age, and gender, to ensure a representative sample within each institution. The inclusion criteria require participants to be physically healthy adults (aged older than 18 years), with access to a smartphone compatible with the mobile web application. Exclusion criteria include significant physical disabilities or medical conditions limiting exercise, based on the Physical Activity Readiness Questionnaire [46], as well as individuals actively participating in competitive sports. The participant assignment procedure will use block randomization to reduce bias and ensure even group distribution, with allocations concealed and blinded from both participants and researchers through a secure system managed by the data specialist team. Data will be stored at a secure server at the University of Concepcion, with backups of the database each hour. A deidentified version of the data and dictionary can be made available upon request.

Since there is no prior evidence regarding effect size for this study, sample size was determined using 1000 simulations, following existing guidelines [47]. Sample sizes were estimated considering the particularities of adaptive experiment design. Simulations based on the relevant populations were conducted using the epsilon-greedy algorithm. Based on simulated data, a sample size of 500 participants during 10 rounds is sufficient to evaluate differences between intervention arms and conduct statistical inference, particularly regarding demographic and behavioral characteristics between participants. The authors are currently working on a publication describing the simulations and associated power analysis, which will become available in late 2025.

To train the reinforcement learning algorithm for the study, initial data are required for which a pilot stage was designed. In this stage, 800 participants will be recruited at one university in order to provide 1 week of activity using the app (two 3-day rounds with a rest day in between). In order to determine the sample size for the pilot, standard power calculation was assumed with a uniform distribution over 3 arms (standard randomized controlled trial). With 665 observations, the pilot is sufficient to detect differences between users. The data from round 1 will be used to estimate the optimal arm for round 2, which will be used for calibration. Participants complete a comprehensive baseline survey eliciting the IBC model as well as several other relevant characteristics (eg, time and risk preferences; see Multimedia Appendix 1) and then are assigned randomly between the 3 difficulty levels for the first round. After completion, participants are compensated for their time. Individuals can opt out from the study at any time.

During the main part of the study, 500 participants will be recruited from multiple sites expecting to participate in a medium-term challenge, completing 10 rounds, equivalent to 39 consecutive days using the app (including rest days). As noted earlier, this provides 5000 unique examples for the algorithm to determine optimal policy over time. Users will be allocated to each arm based on their baseline survey and the trained algorithm during the pilot stage. Regardless of their initial difficulty assignment, each participant will be randomly allocated with equal probability between (1) choice-driven, (2) data-recommended, and (3) data-driven arms. Participants will be compensated for their time, and there will be additional prizes using a lottery mechanism that favors (in probability) those users completing more consecutive workout routines over the course of the study. In both the pilot and main experiment, participants will stay engaged via direct email, push notifications, and social media campaigns.

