## Introduction

Regular physical activity (PA) is essential for maintaining overall health and well-being [1]. Extensive research has demonstrated that consistent exercise is associated with numerous health benefits, including improved sleep quality, enhanced mood, and a reduced risk of noncommunicable chronic diseases such as diabetes, stroke, depression, and dementia. In contrast, physical inactivity has been identified as one of the leading risk factors for premature mortality and a significant contributor to the rising health care costs [2-4]. Despite the well-documented benefits of PA and risks associated with a sedentary lifestyle, 31% of the global adult population—equivalent to 1.8 billion adults—fail to meet the recommended levels of PA [5]. Even with unwavering global efforts from national and international policy, mass media campaigns, and social support and educational programs [6], the number of adults who are physically inactive has been steadily increasing in high-income countries [7].

To address this public health issue, researchers have designed and implemented various interventions aimed at promoting regular exercise adherence, many of which are based on prominent social and psychological theories [8,9], such as theory of planned behavior [10] or self-determination theory [11]. Although these interventions have shown promise in increasing individuals’ intentions to engage in PA, a key challenge lies in translating these intentions into sustained behavior [12,13]. This discrepancy is known as the “intention-behavior gap,” emphasizing that goal intentions only partially materialize on corresponding actions [14]. Studies indicate that individual factors such as lack of motivation and low self-efficacy, as well as environmental barriers, such as time constraints, can hinder individuals from acting on their intentions, even when they recognize the benefits of PA [13,15]. Moreover, these factors are highly heterogeneous across individuals and time. Thus, addressing these challenges requires individualized, flexible, and engaging interventions that consider individual needs, preferences, and contexts, and that promote self-efficacy and focus on closing the intention-behavior gap.

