While machine learning approaches such as CBs offer promise by matching individuals based on their characteristics or context, this optimal recommendation could be seen as a directed action (data-driven), or a recommendation, mediated through individual choice. This is particularly relevant in the context of exercise, where preferences for workout intensity and capabilities to do more demanding exercises can differ widely between individuals [34]. Enabling respondents to choose their workouts, rather than be assigned one through machine learning, respects these diverse preferences and could enhance intervention effectiveness. That is, according to self-determination theory, an influential psychological theory of motivation, being able to choose enhances autonomy, a key driver of intrinsic motivation [35]. Furthermore, evidence suggests that individuals may benefit from a process of self-experimentation to find what works best for them [36]. A meta-analysis shows the potential of choice-based interventions in the context of health behaviours (including exercise), showing improved adherence and reduced dropout across various health behaviors [37]. Past research has found that providing individuals with choice in PA positively influences their perception of exercise [38,39], general well-being [40], as well as adherence to the intervention regime [41]. However, enabling choice is not without risks; individuals may opt for interventions that are ineffective for them due to, for instance, misjudging their own self-control [42] or selecting appealing but ultimately ineffective strategies [43]. Thus, in the context of machine learning–based tailoring, incorporating a “choice” arm allows for the investigation of how algorithmically assigned interventions compare with those selected by individuals themselves, enabling a direct comparison between data-driven assignment of exercise goals versus self-chosen goals.

This study explores three research questions to evaluate the effectiveness of adaptive interventions that focus on goal difficulty and user choice:

Can CBs outperform performance success rate (goal completion) relative to user-chosen workouts?Which user characteristics are most relevant for determining choice probabilities among intervention arms?To what extent does user autonomy in choosing a workout plan influence the effectiveness of recommendations based on CBs?

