## Methods

### Apptivate

For this project, the experiment will be conducted using the web application “Apptivate” [45], extending its initial functionally to incorporate CB algorithms connected to a routine difficulty assignment. Apptivate creates workout routines with 3 different difficulty levels, changing the total workout duration as well as rest times between exercises. PA professionals validated the routine design, ensuring that workouts match recommended guidelines for healthy adults. The overall design allows users to conduct exercises without equipment following the in-app instructions, covering different muscle groups as well as providing both warm-up and stretching exercises.

Apptivate adopts the IBC model for PA [26] as a framework for tailoring workout difficulty recommendations (ie, goals). By leveraging the IBC model, the app ensures that its recommendations address not only dynamic changes in behavior over time but also the psychological factors that influence behavior change. In particular, we capture data on the psychological constructs defined in the IBC model, which are later used as contexts for the algorithm learning process. Participants that take part in the main study will be assigned to 1 of 3 conditions:

Choice-driven: Users select their desired workout difficulty level from a predefined menu. This approach provides users with a sense of autonomy and control over their exercise routine. Choice-driven tailoring leaves the selection of the intervention to the user, allowing individuals to reveal their preferences in a participatory process [33].Data-recommended: The CB algorithm determines optimal workout difficulty (based on user data and the IBC model) and provides a recommendation to the user, but the user retains the option to choose an alternative. This design allows us to investigate the interplay between user autonomy and the effectiveness of data-driven recommendations [27].Data-driven: The CB algorithm automatically recommends workouts based on user data, including contextual features based on the IBC model, without any opportunity to opt into a different difficulty level. This method leverages a machine learning approach to personalize workout plans and potentially optimize user performance (measured as goal completion).

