### Data Collection

Data collection in this study spans multiple dimensions, capturing individual characteristics, app usage patterns, and most importantly, user performance. This multifaceted approach allows us to provide insights on the potential heterogeneous impact of tailored goal-setting interventions.

Baseline survey: Participants will complete an online survey to gather demographic information (eg, age, gender, and socioeconomic status), fitness history (eg, frequency and type of PA), and constructs from the IBC model, such as perceived behavioral control, motivation types (autonomous and controlled), and self-regulatory capacities.Fitness app data: The app will track participant engagement and outcomes, including goal completion rates, total time spent on physical activities, and engagement metrics (eg, frequency of app interactions).Algorithm data: The CB algorithm embedded in the app will collect data on contextual features (eg, user preferences, past performance, and fitness level) and reward functions to predict optimal goals and adapt recommendations over time.

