### Statistical Analysis

Statistical analysis will focus on comparing goal completion rates, engagement metrics, and user satisfaction across the 3 intervention groups. To address missing data, a multiple imputation approach will be applied to ensure robustness in outcome estimates. The primary analysis will estimate the conditional average treatment effect for each intervention arm, with subgroup analyses to identify variations by demographics, baseline fitness, and psychological factors. Mixed-effects models will account for repeated measures and clustering within participants, while sensitivity analyses will assess the robustness of the findings under varying assumptions.

During the pilot phase, multiple CB algorithms will be evaluated based on metrics such as regret minimization (difference between actual and optimal rewards) and balance between exploration and exploitation. The main experiment will focus on estimating the conditional average treatment effect and analyzing differences in goal completion rates and engagement metrics. Subgroup analyses will explore how demographic characteristics (eg, age and gender), motivational factors, and baseline fitness levels influence responsiveness. Metrics such as cumulative reward, prediction accuracy, and contextual feature importance will be analyzed to evaluate the algorithm’s ability to personalize recommendations effectively.

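### Hypothesis 1 concerns the intention-behavior gap, but the stated outcome is completion of a goal whose source differs by arm, so goal completion does not measure the gap

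*Protocol article*

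**What the plan says.** Study Design gives the first main hypothesis as "goal personalization with CBs decreases the intention-behavior gap", with the qualifier that this is for some users. The Introduction explains the gap as the fact that "goal intentions only partially materialize on corresponding actions". A gap therefore has two terms: what the person intended and what the person did.

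The outcome is stated differently. The first research question, at the end of the Introduction, asks "Can CBs outperform performance success rate (goal completion) relative to user-chosen workouts". The Apptivate section equates user performance with goal completion. Statistical Analysis plans on "comparing goal completion rates, engagement metrics, and user satisfaction across the 3 intervention groups". Results describes the main analysis as a comparison of success rates across arms.

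The Apptivate section also says who sets the goal:

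- Choice-driven: "Users select their desired workout difficulty level from a predefined menu".
- Data-recommended: the algorithm proposes a level and the user may take another.
- Data-driven: the algorithm sets the level and the user cannot change it.

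The three levels differ in total workout duration and rest time. Data Collection says the app tracks "goal completion rates, total time spent on physical activities, and engagement metrics (eg, frequency of app interactions".

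**The concern.** The hypothesis names a construct that the stated outcome does not contain. Completing a self-chosen level can reasonably be read as acting on an intention. Completing an imposed level is adherence to the algorithm's target and carries no information on what the user meant to do. In the data-recommended arm it is a mixture. Randomisation balances the people in the arms; it does not give success the same meaning in each.

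The direction of the problem also matters. The Contextual Bandits Algorithm section says the algorithm recommends the option with the best chance of success. Success is the same quantity on which the arms are compared. If easier levels are completed more often, the algorithm can win the comparison by assigning them. One of two main hypotheses could then appear supported although the gap has not narrowed.

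**Working it through.** The point is mainly conceptual and disputes no figure in the protocol. The main-study size of 500 participants over 10 rounds is given without effect size, completion rates, alpha or power, so it cannot be reproduced, and nothing here depends on it being wrong.

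**Step 1: does any section link the hypothesis to a gap measure?**

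| Element | Where | Content |
|---|---|---|
| Hypothesis 1 | Study Design | intention-behavior gap |
| Research question 1 | Introduction | goal completion |
| Performance measure | Apptivate | goal completion |
| Group comparison | Statistical Analysis | goal completion, engagement, satisfaction |
| Main analysis | Results | success rates |
| Psychological constructs of the behavior-change model | Apptivate; Statistical Analysis | algorithm contexts; subgroup factors |
| Total activity time | Data Collection | tracked, but not named in the group comparison |

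No section uses intention as the reference for an outcome.

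**Step 2: can completion rise through difficulty alone?** All inputs here are assumptions.

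- Completion by level (easy/middle/hard) is the same in both arms. Three patterns are tried: 0.70/0.50/0.30, 0.60/0.50/0.40 and 0.55/0.50/0.45.
- Durations are 20/30/40 minutes. Only completed sessions count towards minutes.
- The choice arm uses each level one third of the time. The algorithm arm uses the easiest level 60% to 90% of the time and splits the rest equally.

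Formulas: overall completion = Σ(mix × completion); completed minutes per session = Σ(mix × completion × duration).

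Example, first pattern, 60% easy:

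- Choice completion = (0.70 + 0.50 + 0.30)/3 = 0.50.
- Algorithm completion = 0.6×0.70 + 0.2×0.50 + 0.2×0.30 = 0.58.
- Choice minutes = (14 + 15 + 12)/3 = 13.67.
- Algorithm minutes = 0.6×14 + 0.2×15 + 0.2×12 = 13.8.

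| Completion by level | Easy share | Choice | Algorithm | Difference | Minutes: choice → algorithm | Chance of a significant result |
|---|---|---|---|---|---|---|
| 0.70/0.50/0.30 | 60% | 0.50 | 0.58 | 0.08 | 13.67 → 13.80 | 0.58 |
| 0.70/0.50/0.30 | 90% | 0.50 | 0.67 | 0.17 | 13.67 → 13.95 | 0.997 |
| 0.60/0.50/0.40 | 60% | 0.50 | 0.54 | 0.04 | 14.33 → 13.40 | 0.19 |
| 0.60/0.50/0.40 | 90% | 0.50 | 0.585 | 0.085 | 14.33 → 12.35 | 0.63 |
| 0.55/0.50/0.45 | 60% | 0.50 | 0.52 | 0.02 | 14.67 → 13.20 | 0.08 |
| 0.55/0.50/0.45 | 90% | 0.50 | 0.5425 | 0.0425 | 14.67 → 11.55 | 0.21 |

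The last column uses the protocol's 500 participants, three equal arms and 20% dropout: 500 × 0.8/3 ≈ 133 per arm. With 10 rounds and an assumed within-person correlation of 0.3, the effective size is 133×10/(1 + 9×0.3) = 1330/3.7 ≈ 359 per arm, tested at two-sided 5%. For the first row the chance is 0.85 at a correlation of 0.1 and 0.42 at 0.5.

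**Step 3: what would a common scale look like?** If the gap is baseline intention minus logged behavior, intention measured before randomisation has the same expected mean in every arm. The expected arm difference in the signed gap is then the difference in logged behavior with its sign reversed. Total activity time, which the app already tracks, thus carries the average comparison. The intention item is needed to express a shortfall person by person and to identify the users for whom it shrinks.

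**The case against.** The strongest reply is that the material for a test may already exist. The article says the constructs of the behavior-change model are captured, its list of baseline constructs is open-ended, and the questionnaire in Multimedia Appendix 1 is not shown. Activity time does not depend on who set the goal. A reader might infer that hypothesis 1 cannot be tested at all, or that intention is not recorded during the rounds. The documents support neither: a baseline intention item may exist, context is said to be observed at each round, and the article is silent on intention per round. This part of the reply stands.

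It also stands that the data-recommended arm ends with a user-selected level. Completion there is closer in kind to the choice-driven arm, and that contrast is less affected. Treating a chosen level as the user's intention is an inference, not something the article says.

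A reader might further infer that the trial will announce a narrower gap. The Conclusions and Anticipated Findings make no such claim, and the first research question is already worded as goal completion.

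The reply does not remove the mismatch. This is not detail left to a fuller document: the article states both the hypothesis and the outcome, and the outcome does not measure what the hypothesis names.

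**Conclusion.** The point holds as a mismatch between hypothesis 1 and its stated outcome. Goal completion as written does not measure the intention-behavior gap, and it is least comparable between the data-driven arm and the other two. It does not hold as a claim that the hypothesis is untestable.

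The size is illustrative only. Under the assumed values, a change in difficulty mix raises completion by 2 to 17 percentage points, while completed minutes per session range from a rise of 0.3 to a fall of 3.1. This rests on easier levels being shorter and completed more often, and on the algorithm favouring them; the article gives no durations, rates or mixes. If completion hardly varies by level, the distortion is small, but completion still does not measure the gap.

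**What to change.** Choose one of two routes before the main study starts:

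- **(a)** Restate hypothesis 1 in terms of goal completion and draw no conclusion about the intention-behavior gap from it.
- **(b)** Define the gap on one scale for all three arms: a baseline intention measure, taken before randomisation, against app-logged workouts or total activity time, compared by randomised arm.

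In either case, report total activity time and the assigned or chosen difficulty beside goal completion, so that a gain from easier levels is visible.

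An intention question in each round should be optional at most. From round 2 it is asked after randomisation, so the arm may change the answer, and stating an intention before receiving an imposed level may interact with autonomy, which the study also examines.

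Route (a) costs a change of wording and a narrower claim. Route (b) costs one baseline item, if intention is not already collected, and a little more analysis. Activity time is already logged.

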**Conclusions:**

Physical activity maintenance is key to achieving long term health goals. Tailored digital interventions are promising strategies for physical activity adherence, but personalization often fails to consider dynamic contextual changes. The proposed protocol for a physical activity intervention using adaptive experimentation can provide robust causal inference on the role of choice versus autonomy when goal difficulty is tailored under an adaptive data-driven approach.

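### Hypothesis 2 is worded as mediation through choice, but the three randomised groups identify only pairwise contrasts; H2 and RQ3 should be restated as data-recommended minus data-driven and the causal claims limited to match

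*Protocol article*

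**What the plan says.** All references are to the protocol article.

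- **Hypothesis 2** (Methods, Study Design): "the effectiveness of such goal personalization on behavior is mediated through individual choice". The next sentence presents random assignment to three groups as the means of exploring both hypotheses.
- **Research question 3** (end of the Introduction): "To what extent does user autonomy in choosing a workout plan influence the effectiveness of recommendations based on CBs".
- **Research question 1** (same place): "Can CBs outperform performance success rate (goal completion) relative to user-chosen workouts".
- **The groups** (Methods, Apptivate). Choice-driven: "Users select their desired workout difficulty level from a predefined menu". Data-recommended: the algorithm "provides a recommendation to the user, but the user retains the option to choose an alternative". Data-driven: the algorithm sets the difficulty "without any opportunity to opt into a different difficulty level". Study Design allocates participants to these three with equal probability.
- **A looser use of the same word** (Introduction): "this optimal recommendation could be seen as a directed action (data-driven), or a recommendation, mediated through individual choice".
- **The claims made for the design.** The conclusions of both the Abstract and the Discussion say that it "can provide robust causal inference on the role of choice versus autonomy", in a setting where goal difficulty is tailored. The Apptivate section and Anticipated Findings speak of the interplay between autonomy and recommendations.
- **The analysis** (Statistical Analysis): conditional average treatment effects by arm, mixed-effects models and subgroup analyses. No mediation or interaction estimand is named.

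**The concern.** Whether users may choose is a feature that the trial randomises, so it is not a mediator of the algorithm's effect. The candidates for a mediator are the user's acceptance of the recommendation and the difficulty picked. Both are decided after randomisation and may depend on motivation, so an indirect effect would need assumptions that randomisation does not supply.

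If the hypothesis is read as effect modification instead, it needs the algorithm's effect with choice and its effect without choice. Only the first has a comparator, because no group has neither algorithm nor choice.

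What is at stake is the conclusion. As H2 is worded, a difference between data-recommended and data-driven could be reported as proof that choice makes the algorithm work better, when choice may simply help whatever sets the goal. A difference between data-driven and choice-driven could be credited to the algorithm, when the loss of choice may have added to it or hidden part of it.

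**Working it through.** The plan gives no figure for this point, so there is nothing to reproduce. The check is whether each quantity can be estimated from the three group means.

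**Step 1. Code the groups** (definitions from the Apptivate section).

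| Group | CB | Choice | Expected completion |
|---|---|---|---|
| Choice-driven (CH) | 0 | 1 | a + c |
| Data-recommended (DR) | 1 | 1 | a + b + c + d |
| Data-driven (DD) | 1 | 0 | a + b |
| Not in the trial (m00) | 0 | 0 | a |

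Here a is the completion rate in the absent cell, b the CB effect without choice, c the choice effect without CB, and d the CB-by-choice interaction. Three groups give a design matrix of rank 3 for 4 parameters.

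**Step 2. Sort the contrasts.**

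- DR - CH = b + d: the CB effect when choice is available. Estimable.
- DR - DD = c + d: the choice effect when CB sets or recommends the goal. Estimable.
- DD - CH = b - c: both features change. Estimable, and equal to (DR - CH) - (DR - DD).
- b alone, c alone and d alone: not estimable from the groups.

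So three pairwise contrasts are estimable, two of them independent. DR - DD contains c as well as d. It does not separate a general benefit of choice from a change in how well the algorithm works.

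**Step 3. Show the ambiguity.** Assumed means (the article gives none): CH = 0.50, DR = 0.60, DD = 0.55. The observable contrasts are then fixed: DR - CH = 0.10, DR - DD = 0.05, DD - CH = 0.05. The interaction is d = (DR - CH) - (DD - m00).

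| Assumed m00 | b = 0.55 - m00 | c = 0.50 - m00 | d = 0.10 - b | c + d |
|---|---|---|---|---|
| 0.35 | 0.20 | 0.15 | -0.10 | 0.05 |
| 0.45 | 0.10 | 0.05 | 0.00 | 0.05 |
| 0.55 | 0.00 | -0.05 | +0.10 | 0.05 |

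The trial's data are identical in all three rows, yet choice weakens, leaves alone or strengthens the algorithm's effect. The sizes depend on the assumed means. That d cannot be determined does not.

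**Step 4. Precision of the restated contrast, and the price of the interaction.** The article gives 500 participants, 10 rounds and at most 20% dropout, so about 167 per group, or 133 after dropout. Alpha, power, completion rate and intraclass correlation (ICC) are not stated. I assume two-sided 5%, 80% power, completion 0.5 and ICC 0.2 to 0.6.

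- SD of a participant's mean completion = sqrt(0.25 × (ICC + (1 - ICC)/10)) = 0.265 to 0.400.
- Detectable pairwise difference = (1.96 + 0.84) × SD × sqrt(2/(500/3)) = 0.081 to 0.123; with 400 completers, 0.091 to 0.137.
- Detectable interaction if a fourth cell were added at the same total = (1.96 + 0.84) × SD × sqrt(4/(500/4)) = 0.133 to 0.200; with 400 completers, 0.148 to 0.224.
- The ratio is 1.63. Equal precision would need (4 × 4)/(2 × 3) = 2.67 times the participants.

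**The case against.** The strongest reply is that the article explains its own phrase. In the Introduction, a recommendation mediated through choice is one that the user may override, as opposed to one that is imposed. Read that way, H2 and RQ3 ask how data-recommended compares with data-driven, a concurrent randomised contrast. RQ3 does not say that effectiveness must be an increment over a control with neither feature. The causal claim in the conclusions is also made for a setting where difficulty is already tailored. All of this stands. It shows which contrast the hypothesis should name, but a main hypothesis should not leave the reader to choose between an identified and an unidentified meaning.

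Three further points stand:

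- Data-driven versus choice-driven is deliberate. The Introduction presents it as a direct comparison of assigned with self-chosen goals, and it is a valid randomised answer to RQ1.
- No mediation analysis, and no conditioning on acceptance, is planned. The absence of one from an article is not a fault.
- The limit applies to between-group contrasts. If the algorithm explores with known, logged probabilities, reweighting within the data-driven group might approximate a non-personalised policy without choice. The article fixes neither the algorithm nor its exploration. Pilot round 1 assigned difficulty at random, but at one university, briefly and not concurrently.

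A reader might infer that H2 and RQ3 cannot be answered at all, that only two contrasts can be estimated, or that a fourth group is required. The documents do not support these readings: three pairwise contrasts are estimable, and one of them answers H2 and RQ3 in the article's looser sense.

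**Conclusion.** The point holds as a fault in how the hypothesis and the causal claims are stated, not in the randomisation, the arms or the sample size. Group randomisation identifies the effect of adding a CB recommendation when choice is available, the effect of retaining choice when CB is used, and the combined change between data-driven and choice-driven. It identifies neither mediation through choice nor a CB-by-choice interaction. In the illustration, one set of observed means fits an interaction anywhere from -10 to +10 points. Those sizes rest on assumed means, whereas the failure of identification follows from the group definitions alone.

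The change is worth making before the main study because it alters what the trial may conclude: data-recommended minus data-driven should not be reported as a change in the algorithm's effectiveness, nor data-driven minus choice-driven as the algorithm's effect alone.

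**What to change.** Keep the three groups and change the wording:

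1. Restate H2 and RQ3 as data-recommended minus data-driven, the effect of retaining choice given CB recommendations, and drop the term for mediation.
2. Keep data-driven minus choice-driven as the RQ1 comparison of assigned with self-chosen goals, and state that it changes algorithm and choice together.
3. Name data-recommended minus choice-driven as the contrast for H1, which isolates adding the CB recommendation with choice held constant.
4. Limit the causal and interplay claims (Abstract Conclusions, Apptivate, Anticipated Findings, Discussion Conclusions) to these contrasts, and say that the randomised groups do not identify the between-group interaction.
5. Report acceptance of recommendations descriptively.

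The cost is a set of text edits and narrower claims. Arms, allocation and the 500 participants are unchanged. If the interaction itself were wanted, it would need a fourth cell and about 2.67 times the participants for the precision of a pairwise contrast.
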